### Strategies to improve adherence to intervention

After starting the intervention, online video calls (WhatsApp or Viber) will be made to caregivers of the selected elderly care institution on a daily basis. The first call will be made to remind participants to ingest either treatment (200 mL of Entrasol Platinum) or control (200 mL of water), after dinner. A second call will be made to make sure whether all participants in the intervention group have consumed the supplement and all the participants in the control group have consumed an equal quantity of water. There will be random visits from the data collection team during the administration of ONS.

Compliance with ONS intake will be calculated over 12 weeks (84 days) using the participant's intake record and return of balance product containers. The percentage of compliance will be calculated by the following formula:

The number of supplement containers consumed is divided by the number of supplement containers instructed to consume, multiplied by 100.

### Relevant concomitant care permitted or prohibited during the trial

Concomitant care apart from the consumption of ONS in the intervention group will be routine care during monthly clinic visits, which includes medication review. Both participants in the intervention and control groups will follow their usual dietary behaviors. Neither their habitual dietary intake nor lifestyle will be altered by the intervention.

### Provisions for post-trial care

We do not expect any adverse effects since the ONS (Entrasol Platinum) used in this study is a locally and internationally marketed product, with no adverse effects reported in post-market surveys. After the intervention period, participants will be screened for malnutrition. If the intervention group derives a benefit by improving nutritional status, the control group will be provided with the ONS after the 12 weeks of the study for 3 months. If the malnutrition status of participants does not improve or worsens, participants will be referred for specialist consultation and management.

### Outcomes

The primary outcome measure is the percentage of intervention group participants who achieved at least 5% weight gain compared to the control group.

The secondary outcome measures include mean between-group differences of the following variables from baseline to the end of the 12th week:

I.Anthropometric measurementsBody weightHeightBody mass index (BMI)Mid-upper arm circumference (MUAC)Calf circumference (CC)Waist circumferenceTriceps skin fold thicknessII.Body compositionDXA lean body mass and fat massIII.Biochemical parametersFull Blood Count (FBC)Hs-CRP (C-reactive protein)Serum albuminTotal cholesterolSerum total 25-hydroxy vitamin DIV.Functional capacityHand grip strengthKnee extensionActivities of daily living — Barthel indexV.FrailtyFive fried model indicatorsVI.Respiratory muscle strength (peak expiratory flow rate)VII.Energy and macronutrient intake per dayVIII.Cognitive status (Montreal Cognitive Assessment)IX.Physical activity levelPhysical Activity Scale for the Elderly (PASE)International Physical Activity Questionnaire (IPAQ – short form)

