## Objectives

### Hypothesis

Providing an ONS for 12 weeks will increase the body weight of institutionalized older adults with malnutrition or at risk of malnutrition at least by 5%.

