### Sample size

The sample size calculation was based on studies indicating that a weight gain of 5% can be expected with an ONS intervention, and is sufficient to achieve an overall improvement in nutritional status [23]. A clinically relevant difference was defined as an increase in this fraction to 75% or greater in the treatment arm. Hence, a total of 50 adults will be recruited for the study (alpha, 5%; beta, 10%; drop-out rate, 20%) after the screening for eligibility against inclusion/exclusion criteria. Then, participants will be randomly assigned into two groups (*n*=25 intervention and *n*=25 control). The formula used for sample size calculation was as follows:$${n}_{B} =\left( \frac{{p}_{A \left( 1- {p}_{A}\right)}}{k} \right)+{\left(\frac{z1- \frac{\propto }{2 } + z1- \beta }{{p}_{A-{P}_{B}}}\right)}^{2}$$$${n}_{B}$$ = Sample size in one arm

*P*_*A*_ = Proportion of participants expected to achieve 5% improvement in body weight in the control group (0.3) [23]

*P*_*B*_ = Proportion of participants expected to achieve 5% improvement in body weight in the intervention group (0.75) [23]

*Κ* = Sampling ratio (1:1)

*Z*_*α*_ = Critical value of the normal distribution at *α* (*α* is 0.05 and the critical value is 1.96)

*Z*_*β*_ =Critical value of the normal distribution at *β* (*β* is 0.1)

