### Anthropometric measurements

Anthropometric and body composition measurements will be taken by trained data collectors using calibrated equipment according to international recommendations.

Weight: body weight will be measured using the calibrated scale (Seca 813, Hamburg, Germany), to the nearest 0.1 kg using a digital weighing scale with participants wearing light clothing.Height: Height will be taken to the nearest 0.1 cm, as the maximum distance to the uppermost position on the head from heels, with the individual standing barefoot and following full inspiration using a stadiometer (Seca 213 portable stadiometer).BMI: Based on the values of weight and height, BMI will be calculated.Mid-upper arm circumference (MUAC): The midpoint between the acromion and the olecranon process in the non-dominant arm will be marked when the right elbow is 90° flexed placing the forearm palm down across the trunk. The measurement will be taken using a plastic flexible tape (Seca 201, Germany) to the nearest 0.1 cm when the arm is extended alongside the body with the palm facing upwards.Calf circumference (CC): The largest circumference of the calf of the non-dominant leg will be measured using a plastic flexible tape (Seca 201, Germany) to the nearest 0.1 cm in a seated/supine position when the knee and hip are 90° flexed in the two lower limbs.

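### Cutting weight change at 5% discards information, and at 20 evaluable per arm the binary primary comparison has about 73–82% power, not the stated 90%

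*Protocol article*

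**What the plan says.** The primary outcome in the Outcomes section is a responder percentage: "The primary outcome measure is the percentage of intervention group participants who achieved at least 5% weight gain compared to the control group". Mean change in body weight is kept, but as the first item on the secondary list: "The secondary outcome measures include mean between-group differences of the following variables from baseline to the end of the 12th week". Weight is measured "to the nearest 0.1 kg using a digital weighing scale" (Anthropometric measurements), and Table 2 schedules it at baseline, week 4 and week 12 for both arms.

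The Hypothesis reads "Providing an ONS for 12 weeks will increase the body weight of institutionalized older adults with malnutrition or at risk of malnutrition at least by", and the figure it names is the same threshold, 5%. The Sample size section gives the reason for the threshold, namely that "a weight gain of 5% can be expected with an ONS intervention, and is sufficient to achieve an overall improvement in nutritional status". It then assumes that 30% of controls and 75% of the intervention arm reach 5%, with alpha 5% (critical value 1.96), beta 10% and drop-out 20%. The result is 50 participants, 25 per arm. The Statistical methods section names a paired t-test, multiple regression for weight change and the Mann-Whitney test. It names no test for comparing the two responder percentages.

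**The concern.** Under a yes/no rule, a gain of 4.9% counts the same as a loss, and a gain of 5.1% the same as one of 12%. In a trial of 50 people that lost information matters, and the finer measurement is already being taken.

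Separately, the stated 90% power comes from a large-sample formula applied to about 20 people per arm, where such formulas are least reliable. If true power is well below 90%, the trial has a larger chance than readers are told of missing the effect it was designed to detect, while the weights already collected might have shown it.

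**Working it through.** **Inputs.** From the Sample size section: pA = 0.30, pB = 0.75, two-sided alpha 0.05, power 90%, drop-out 20%, 25 per arm. Derived here: 25 × 0.8 = 20 evaluable per arm. Not given anywhere: the SD or shape of the distribution of percent weight change.

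**Step 1: the plan's own figure.** The printed formula is typographically broken. Its standard unpooled form is

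n = [pA(1−pA) + pB(1−pB)] × [(1.96 + 1.2816)/(pA − pB)]²
= (0.21 + 0.1875) × (3.2416/0.45)² = 20.63 per arm.

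Multiplying by 1.2 gives 24.75, so 25 per arm and 50 in total. The stated size is reproduced. Dividing by 0.8, which would leave 20.63 evaluable after a 20% loss, gives 25.8, so 26 per arm.

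**Step 2: that formula at 20 per arm.** Power = Φ(0.45/√(0.3975/20) − 1.96) = 89.1%. The matching unpooled Wald test, by full enumeration, also has 89.1% power, but its true type I error reaches about 8%.

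**Step 3: exact power of the usual tests.** These sum the two binomial distributions over all outcome tables, at 30% versus 75%:

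| Evaluable per arm | Fisher | Chi-square (uncorrected) |
|---|---|---|
| 20 (20% lost) | 73.1% | 82.3% |
| 24 (about 5% lost) | 85.7% | 91.5% |
| 25 (none lost) | 88.1% | 93.1% |

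Boschloo's test at 20 per arm gives 81.6%. Fisher's test first reaches 90% at 29 evaluable per arm.

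**Step 4: where the gap to 90% comes from.** Having 20 evaluable rather than 20.63 costs about 0.9 points (90 − 89.1). Going from the unpooled approximation to the actual test costs a further 6.8 points for chi-square (89.1 − 82.3) or 16.0 for Fisher (89.1 − 73.1).

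**Step 5: the same data on the continuous scale.** Assume percent weight change is normal with equal SDs. Then 30% and 75% above a common cut imply a standardised difference of z(0.75) − z(0.30) = 0.674 + 0.524 = 1.199. An unadjusted two-sample t-test at 20 per arm has 95.9% power, which is 13.6 points above chi-square and 22.8 above Fisher.

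**Step 6: sensitivity to that assumption.** Simulated power at 20 per arm, with responder rates held at 30% and 75%:

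| Shape of weight change | t-test | Mann-Whitney |
|---|---|---|
| Normal, SD ratio 0.67–1.5 | 94–96% | 93–95% |
| Skewed (gamma), SD ratio 0.67–1.5 | 81–95% | 90–97% |
| Heavy tails (t with 3 df, Laplace), SD ratio 0.67–1.5 | 72–76% | 82–88% |
| Heavy tails (t with 5 df), equal SD | 87% | 92% |

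At the worst of these the mean comparison is no better than Fisher on the cut, and the rank test only equals chi-square.

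**The case against.** The strongest reply is that the trial was deliberately sized on a responder percentage with a clinical reason for the threshold: a 5% gain "is sufficient to achieve an overall improvement in nutritional status". The Hypothesis names the same 5%. A reader might infer that outcome and hypothesis conflict. The documents do not support that: the two differ in form (amount gained against share of responders) but share the threshold. Whether the cited source justifies 5% cannot be judged from the protocol.

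A reader might also infer that the cut takes power from 96% to 73–82%. That goes too far. No 96% design was ever planned, the 96% needs near-normality, and a responder outcome sized by exact calculation would also reach 90%. Against the stated 90%, the formula and the drop-out inflation are at work, as Step 4 shows.

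A third tempting inference is that 5% is the expected mean gain, so only about half the supplement arm would pass the cut. Against 30% in controls, power at 20 per arm would then be 16% (Fisher) to 25% (chi-square), and 37% for the mean comparison. The wording permits this reading, but the same section sets the proportion at 0.75. It is one scenario, not the plan's assumption.

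It is fair to add that the missing-data section expects under 5% missing for the primary outcome, so 20 per arm may prove pessimistic. It is nevertheless the number left by the plan's own 20% drop-out. Finally, mean weight change is already a secondary outcome, and changing a registered primary outcome after recruitment has begun in an open-label trial can look like outcome switching. That last point stands, and it weighs on which version of the fix to choose.

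**Conclusion.** The point holds in a limited form. The binary primary outcome discards information from a precise measurement. At 20 evaluable per arm its power is about 73% (Fisher) to 82% (chi-square) against a stated 90%, and 88–93% with no drop-out. These figures rest only on the plan's own 30%, 75% and 20%.

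The advantage of the continuous scale is conditional. It is about 96% if percent weight change is roughly normal with similar SDs. Under heavy tails a mean comparison can fall to about 75%, while a rank test gives about 82–92%. The documents supply nothing to decide between these. The result does not show that the 5% threshold is clinically wrong, nor that the whole shortfall from 90% is caused by using it.

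**What to change.** 1. **Sample size section.** Restate the power of the binary comparison at 20 evaluable per arm for a named test, and name that test in the Statistical methods section. If 90% were to be kept with Fisher's test, 29 evaluable per arm would be needed, or 29/0.8 = 36.25, so 37 randomised per arm.

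2. **Outcomes and Statistical methods sections.** Before any unblinded look, pre-specify a full-scale analysis of percent weight change from baseline to week 12, adjusted for baseline weight, with a 95% CI and a rank-based check for non-normality. Then choose one of two uses:
   - make it the primary comparison, with the proportion gaining at least 5% as first secondary outcome; or
   - keep the responder percentage primary, estimate each arm's proportion at or above 5% from the fitted model with a bootstrap CI for the difference, and report the raw proportions as a check.

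**Cost.** No extra participants, visits or measurements are needed for the second item. Both uses need a dated, documented protocol and registry amendment, with matching wording in the Abstract, in an open-label trial that has been recruiting since February 2023. The first changes the registered primary outcome and must be justified openly. The second keeps it but relies on an approximate distribution for weight change.

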### Participant timeline

At baseline and the end of the 12-week intervention period, dietary (24-h dietary recall), anthropometric (weight, body mass index (BMI), MUAC, calf circumference, waist circumference), biochemical (full blood count, serum C-reactive protein, serum albumin, total cholesterol, and serum total 25-hydroxy vitamin D), functional (hand grip strength, knee extension, and Barthel index), frailty (five fried model indicator score), cognitive (Montreal Cognitive Assessment Score), physical activity (Physical Activity Scale for the Elderly and International Physical Activity Questionnaire), body composition (skin fold thickness and dual-energy X-ray absorptiometry scan), and respiratory muscle strength data will be collected. Participants will be followed up at the end of the 4th week of the intervention only for dietary (24-h dietary recall), anthropometric (weight, body mass index (BMI), MUAC, calf circumference, waist circumference), functional (hand grip strength. knee extension) and body composition (skin fold thickness) outcomes. Details of the study schedule are given in Table 2.

**Table 2 Tab2:** Schedule of enrolment, interventions and assessments

**Timepoint**	**Study period**		
	**Enrolment baseline** ***T***_***0***_	**Intervention period (Time in weeks)**	
		***4w*** ***Follow-up***	***12w***
**Enrollment**			
Mini Nutrition Assessment	X		X
Eligibility screen	X		
Informed consent	X		
Allocation	X		
**Study arms**			
Intervention group	X	X	X
Control group	X	X	X
**Assessments**			
*Sociodemographic characteristics*	X		
*Body weight*	X	X	X
*Height*	X		
*Mid-upper arm circumference*	X	X	X
*Calf circumference*	X	X	X
*Waist circumference*	X	X	X
*Triceps skin fold thickness*	X	X	X
*Dual-energy X-ray absorptiometry (DXA)*	X		X
*Blood parameters (FBC, serum albumin, total cholesterol, Hs- CRP, total 25-hydroxy vitamin D)*	X		X
*Hand grip strength*	X	X	X
*Knee extension*	X	X	X
*Activities of daily living (Barthel index)*	X		X
*Five fried model indicators*	X		X
*Respiratory muscle strength*	X		X
*Blood pressure*	X		X
*Dietary assessment (24-h dietary recall)*	X	X	X
*Cognitive assessment (MoCA)*	X		X
*Physical Activity Scale for the Elderly (PASE) score*	X		X
*International Physical Activity Questionnaire (IPAQ) score*	X		X

*MoCA* Montreal Cognitive Assessment, *FBC* Full blood count, *CRP* C-reactive protein

### Sample size

The sample size calculation was based on studies indicating that a weight gain of 5% can be expected with an ONS intervention, and is sufficient to achieve an overall improvement in nutritional status [23]. A clinically relevant difference was defined as an increase in this fraction to 75% or greater in the treatment arm. Hence, a total of 50 adults will be recruited for the study (alpha, 5%; beta, 10%; drop-out rate, 20%) after the screening for eligibility against inclusion/exclusion criteria. Then, participants will be randomly assigned into two groups (*n*=25 intervention and *n*=25 control). The formula used for sample size calculation was as follows:$${n}_{B} =\left( \frac{{p}_{A \left( 1- {p}_{A}\right)}}{k} \right)+{\left(\frac{z1- \frac{\propto }{2 } + z1- \beta }{{p}_{A-{P}_{B}}}\right)}^{2}$$$${n}_{B}$$ = Sample size in one arm

*P*_*A*_ = Proportion of participants expected to achieve 5% improvement in body weight in the control group (0.3) [23]

*P*_*B*_ = Proportion of participants expected to achieve 5% improvement in body weight in the intervention group (0.75) [23]

*Κ* = Sampling ratio (1:1)

*Z*_*α*_ = Critical value of the normal distribution at *α* (*α* is 0.05 and the critical value is 1.96)

*Z*_*β*_ =Critical value of the normal distribution at *β* (*β* is 0.1)

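### The printed sample-size formula is wrong and the 20% drop-out allowance falls slightly short, so the 90% power should be restated with the test it refers to

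*Protocol article*

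**What the plan says.** All the inputs are in the Sample size section of the protocol article.

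- Error rates and drop-out: "a total of 50 adults will be recruited for the study (alpha, 5%; beta, 10%; drop-out rate, 20"%). The two-sided value is confirmed by the note on alpha, which "is 0.05 and the critical value is 1.96".
- Control arm, pA: "Proportion of participants expected to achieve 5% improvement in body weight in the control group (0.3").
- Intervention arm, pB: "Proportion of participants expected to achieve 5% improvement in body weight in the intervention group (0.75").
- Allocation, k: "Sampling ratio (1:1").
- Result: "participants will be randomly assigned into two groups (*n*=25 intervention and *n*=25 control").

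The section introduces its expression with "The formula used for sample size calculation was as follows". As printed, the expression is pA(1−pA)/k **plus** the square of (z for 1−α/2 + z for 1−β)/(pA−pB). No pB(1−pB) term appears.

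Two other sections bear on the point. Statistical methods for primary and secondary outcomes names no test for comparing the two proportions. The section on non-adherence and missing data expects less than 5% of primary-outcome data to be missing.

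**The concern.** The expression is presented as the one used, yet it cannot give the planned number. A variance has to multiply the squared z-ratio. Added to it, it contributes only a fraction of one participant, and the second arm's variance is ignored altogether.

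The step from the required number to the recruited number also looks off. If a fifth of participants are lost, 25 per arm become 20, one fewer than the 21 that the intended formula requires.

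This is the only justification given for the size of the trial on its primary outcome. A reader cannot reproduce the 90% from the page or tell which analysis it refers to. With arms this small, the choice of test changes the power noticeably.

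**Working it through.** **Inputs.** pA = 0.30, pB = 0.75, difference 0.45, two-sided alpha 0.05 (z = 1.96), beta 0.10, k = 1, drop-out 20%, all from the Sample size section. The protocol does not print the z-value for beta; the standard normal value is 1.2816.

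**Common terms.**
- Squared z-ratio: ((1.96 + 1.2816)/0.45)² = 51.89
- pA(1−pA) = 0.30 × 0.70 = 0.21
- pB(1−pB) = 0.75 × 0.25 = 0.1875

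**1. Formula as printed.** 0.21 + 51.89 = 52.10, so 53 per arm before drop-out. This does not give 25.

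**2. Usual unpooled formula.** n = (pA(1−pA)/k + pB(1−pB)) × squared z-ratio = (0.21 + 0.1875) × 51.89 = 0.3975 × 51.89 = 20.63, so 21 per arm.

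**3. Reproducing the planned 25.** 20.63 × 1.2 = 24.75, so 25 per arm and 50 in total. This matches the protocol exactly, so the unpooled formula with a 1.2 multiplier is very probably what was used.

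**4. Drop-out by division.** 20.63/0.8 = 25.8, so 26 per arm (52 in total). If n is first rounded up, 21/0.8 = 26.25, so 27 per arm (54 in total).

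**5. Power for 75% against 30%.** With full drop-out, 25 × 0.8 = 20 per arm remain. With under 5% missing, 25 × 0.95 = 23.75, so about 24 per arm. The chi-square (no continuity correction) and Fisher figures come from exact enumeration of all pairs of binomial outcomes, rejecting when the two-sided p-value is below 0.05.

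| Completers per arm | Unpooled approximation | Chi-square | Fisher exact |
|---|---|---|---|
| 20 | 89.1% | 82.3% | 73.1% |
| 21 | 90.5% | 85.1% | 75.7% |
| 24 | 93.8% | 91.5% | 85.7% |
| 25 | 94.6% | 93.1% | 88.1% |

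**6. Does the unpooled test hold its alpha?** At 20 per arm the unpooled z-test also has an exact power of 89.1%. Its true two-sided type I error, enumerated for common proportions from 0.20 to 0.75, is 6.5% to 8.1%. The chi-square test runs from about 4.3% to 5.3% over the same range. Part of the unpooled test's advantage in power is therefore bought by exceeding the stated 5%.

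**The case against.** The strongest reply is that the misprint did not produce the sample size. The standard formula with the protocol's own inputs gives exactly 25 per arm, so the printed expression is most likely an equation-editing slip. This stands. A reader might infer from the printed formula that the trial needs more than twice its planned size. The documents do not support that, because 53 per arm is the output of a misprint and not a requirement of the design.

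A reader might also infer that 50 participants simply fail to deliver 90% power. That is too strong, for three reasons:

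- By the method evidently used, 20 completers per arm give 89.1%, about one point short.
- The larger shortfalls depend on choosing a chi-square or Fisher test. The protocol article does not fix the test and may leave it to an analysis plan that is not shown.
- They also depend on the full 20% loss. The protocol elsewhere expects under 5% missing, and at about 24 per arm the chi-square test exceeds 90%.

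These points limit the finding without removing it. The formula is still wrong and the multiplier still falls short of its purpose. The Sample size section itself plans for a 20% loss and a 5% alpha, and the 89% comes from a test whose true error rate reaches about 8% at that size. Nor does the under-5% expectation settle the matter, since it sits uneasily with the 20% in the sample-size statement.

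**Conclusion.** The point holds, at moderate severity. Two errors are certain: the printed formula gives 53 per arm instead of 25, and multiplying by 1.2 falls short of what a 20% loss requires by 1 to 2 participants per arm (2 to 4 in total).

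The effect on power is conditional. Given true proportions of 30% and 75% and the full 20% loss, power is about 89% by the unpooled approximation, 82% for chi-square and 73% for Fisher. With about 24 completers per arm it is about 92% for chi-square and 86% for Fisher. An unqualified 90% is therefore not a sound statement of the design's power, but neither the planned total nor the conduct of the trial has to change because of it.

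**What to change.** Make three changes in the Sample size section, keeping the total at 50.

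1. Replace the formula by n = (pA(1−pA)/k + pB(1−pB)) × ((z for 1−α/2 + z for 1−β)/(pA−pB))², and show the result, 21 per arm.
2. State the drop-out allowance as n/(1 − 0.20), which gives 26 to 27 per arm, and say that 25 per arm is retained.
3. Replace the unqualified 90% by the power at 20 completers per arm, together with the test it refers to. Possible wording: *Fifty participants leave 20 per arm after 20% drop-out. For 75% against 30% at a two-sided 5% level, this gives about [power] with [test].* The entries are about 89% for the unpooled approximation, 82% for the uncorrected chi-square test and 73% for Fisher's exact test. If the unpooled figure is chosen, add that the test's true type I error can reach about 8% at this size.

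The power under the expected level of missing data (about 24 per arm: 92% chi-square, 86% Fisher) can be given beside it.

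The cost is a change of wording and, unless the unpooled figure is kept, a less favourable power figure. No participants are added.
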